### Transformations

We will use simple coding for the following categorical variables:

- Income
- Education
- Race

The variable "Diet" will be a dummy variable that takes the value of 0 if participants responded no / not applicable, and the value of 1 if any of the other options is selected.

### Inference Criteria

We will use the standard  $p < .05$  criteria for the models to determine if the models suggest that the results are significantly different from those expected in the null hypothesis were correct. We will use the Hosmer-Lemeshow test to assess how well the model predicts the dependent variable. In addition, we will use AIC, BIC, log-Likelihood, and  $p^2$  (rho square) to determine the fit of the models. Given the multiple trust indices that we are measuring, we will test for multicollinearity with Variance Inflation Factors (VIF).

We will use statistical tests, such as paired t-tests and ANOVA, to identify the differences between before and after the implementation of the label in the snacks. The same test will be applied to identify differences between treatment results.

### Data Exclusion

We will verify that each participant answered each of the twelve choice scenarios for the three treatments. Straightlining: If found that participant will be excluded from the survey. Outliers will be included in the analysis.

47  
48 **Missing Data**  
49

50 If a participant doesn't answer any of the twelve choice scenarios, and / or answer the trust-related  
51 questions, that participant will not be included in the analysis.  
52

53 **Exploratory Analysis**  
54

55 If the institutional trust index doesn't predict the probability of choosing a healthy snack labeled with a  
56 Food Compass Score, we will explore the effect of interpersonal trust or generalized trust in the logistic  
57 regression.  
58

59 If the index measuring trust in the government doesn't predict the probability of choosing an FDA-  
60 healthy snack, we will explore the effect of interpersonal trust or institutional trust in the logistic  
61 regression.

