## **2.0 Background / Literature Review / Rationale for the study:**

The U.S. Food and Drug Administration (FDA) announced in 2016 that it would begin redefining “healthy” food labels, in part spurred by a dispute with KIND Snacks about its use of the term on KIND Bar packaging. The lack of an updated regulatory definition of the term has left food companies like KIND vulnerable to class action and consumers vulnerable to confusing or misleading food labels. The FDA, however, has made no regulatory decisions since the initial 2016 request for information. In the interim, the FDA has held a public meeting on the redefinition, updated its Nutrition Innovation Strategy to include defining the term, and got approval from the Office of Management and Budget (OMB) to create a focus group review of a “healthy” icon on food packages. Most recently, OMB approved another proposal from the FDA to redefine the term and produce additional research on developing a “healthy” front-of-package (FOP) icon. However, no research evaluating the impact of a “healthy” label, particularly one endorsed by the FDA, currently exists in a U.S. population.

The influence of an FDA-endorsed “healthy” label on food choice is also presumed to interact with the level of trust participants have in food-related institutions like the FDA. Survey questions of attitude-based trust questions (e.g., “generally speaking, would you say that most people can be trusted or that you can’t be too careful in dealing with people?”) have shown varying relationships with choice.

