## **18.0 Provisions to Protect the Privacy and Confidentiality of Participants and the Research Data:**

Participation in the survey is entirely voluntary. Participants are reminded that they may leave blank any questions they do not wish to answer. Questions do not contain information of a sensitive or personal nature. Participants may skip individual questions, but a complete response will require a response to the choice experiment task questions. Participants will interact with the Tufts team members facilitating the survey's implementation, but no personal information will be provided.

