## Analysis Plan

### Statistical Models

We will run the following models to test our hypothesis.

- A binary logistic regression to assess the proportion of participants that choose healthy and unhealthy snack choices. The main predictor variable is the presence of an FDA Healthy, Healthy, or Food Compass Score. Other predictor variables to analyze are generalized trust, personal trust, institutional trust and trust in the government, knowledge, physical activity levels, diet, and sociodemographics.

We will run the same model for each treatment to test, for example, hypothesis H2.

- We plan to run a multinomial logit model (MNL), random parameter model (RPL), random parameter model with EC (RPL-EC), and latent class analysis (LCA) to investigate participants' willingness to pay on each treatment. We will use the presence of a healthy label or food compass score, and price as the main attributes of the utility function for the MNL, RPL, RPL-EC and LCA. However, for the LCA we will use generalized trust, personal trust, and trust in the government (according to hypothesis H2) as consumers' characteristics for the segment membership function.

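### The exclusion for unanswered trust questions should apply only to the models that use trust, not to the label and willingness-to-pay analyses

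*Combined protocol and SAP*

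**What the plan says.** The rule is in the Missing Data paragraph of the Analysis Plan, under Data Exclusion: "If a participant doesn't answer any of the twelve choice scenarios, and / or answer the trust-related" ... "questions, that participant will not be included in the analysis". It names no model to which it does or does not apply. It gives no imputation, no sensitivity analysis and no comparison of excluded with retained participants.

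Section 18.0 tells participants something different: "Participants are reminded that they may leave blank any questions they do not wish to answer". It then sets the standard for completeness: "Participants may skip individual questions, but a complete response will require a response to the choice experiment task questions". That section has no separate Phase 2 text, so this is the only statement on skipping.

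Statistical Models shows where trust is used:
- For the multinomial logit, the two random-parameter models and the latent class analysis: "We will use the presence of a healthy label or food compass score, and price as the main attributes of the utility function".
- Among these choice models, trust is added only to the latent class analysis, to explain class membership: "However, for the LCA we will use generalized trust, personal trust, and trust in the government".
- In the binary logistic regression the label is the main predictor, and trust is one of several others: "Other predictor variables to analyze are generalized trust, personal trust, institutional trust and trust in the government".

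The paired t-tests and ANOVA under Inference Criteria compare label conditions and treatments. No trust variable is mentioned for them.

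Section 2.0 gives trust its scientific role. The influence of an FDA-endorsed label "is also presumed to interact with the level of trust participants have in food-related institutions like the FDA".

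**The concern.** A participant can make every incentivised choice, count as complete under Section 18.0, and still be removed under the Analysis Plan for leaving trust questions blank. For a model that conditions on trust, that is ordinary complete-case handling. For a model built on label and price, the missing answer is not needed and the person's choices are usable.

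Two things are at stake. The first is precision in the analyses that address the label's effect on snack choice and willingness to pay. The second is the population those estimates describe. The rule selects on having answered the trust questions. If answering is related to trust, and trust modifies the label effect as the Background presumes, the average label and willingness-to-pay estimates move towards the kind of person who answers. The plan has no step that would reveal this.

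**Working it through.** **The plan's own figure.** Section 5.2 gives a Phase 2 sample of up to 400, with 350 to 400 expected, justified by saturation of feedback and error detection. There is no effect size, power or allowance for missing data, so the figure cannot be reproduced by formula. It is used below only as the starting N.

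**Step 1: which analyses need trust answers.**

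| Analysis | Trust variable listed? | Trust-item exclusion needed? |
|---|---|---|
| Multinomial logit and both random-parameter models | No | No |
| Paired t-tests and ANOVA on label and treatment | No | No |
| Binary logistic regression with trust predictors | Yes | Yes, for a complete-case fit |
| Latent class analysis | Yes, for class membership | Yes, for a complete-case fit |

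**Step 2: cost in precision.** Let d be the share excluded for missing trust answers (assumed; not in the documents). Retained N = 400 × (1 − d). With participants as the independent units, standard errors grow by the factor 1/√(1 − d).

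- d = 5%: 400 × 0.95 = 380; 1/√0.95 = 1.026, so +2.6%.
- d = 10%: 400 × 0.90 = 360; 1/√0.90 = 1.054, so +5.4%.
- d = 20%: 400 × 0.80 = 320; 1/√0.80 = 1.118, so +11.8%.

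At 8 choice scenarios each (the figure given first in the Phase 2 procedures), the choices discarded are 20 × 8 = 160, 40 × 8 = 320 and 80 × 8 = 640. At the twelve scenarios named in the Analysis Plan they are 240, 480 and 960. Keeping 400 analysable would require 400/0.95, 400/0.90 or 400/0.80, that is 422, 445 or 500 participants, all above the stated maximum.

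**Step 3: dependence on the trigger.** If one blank item were enough to exclude, and each of k items were skipped independently with probability 2%, the share excluded would be 1 − 0.98^k: 7.8% for k = 4, 14.9% for k = 8 and 21.5% for k = 12. If all items had to be blank, the share would be far smaller. The documents give neither the trigger nor the number of items.

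**Step 4: possible shift in the label estimate.** For illustration, assume half the sample has low trust with a label effect of 0.02 on the probability of a healthy choice, and half has high trust with 0.12. The true average is 0.07. With skip rates s_L and s_H, the estimate among those retained is

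[0.5(1 − s_L) × 0.02 + 0.5(1 − s_H) × 0.12] / [0.5(1 − s_L) + 0.5(1 − s_H)].

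- 10% and 10%: 0.063/0.90 = 0.0700, no shift.
- 10% and 2%: 0.0678/0.94 = 0.0721, +3%.
- 20% and 5%: 0.065/0.875 = 0.0743, +6%.
- 30% and 5%: 0.064/0.825 = 0.0776, +11%.

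The effects, the even split and the skip rates are all assumptions. The calculation shows that a shift needs both differential skipping and a label effect that differs by trust.

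**The case against.** The strongest defence is that one common sample has a purpose. The plan judges fit by AIC, BIC and log-likelihood across several choice models, and those criteria can be compared only when the models are fitted to the same participants. This stands. It argues for making those comparisons on a common subset, not for estimating every willingness-to-pay model on it.

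It is also fair that skipping may be rare. The survey is taken at a staffed table, and Section 18.0 describes the questions as not sensitive. The sample is a store-intercept convenience sample without quotas, so some further selection is a secondary matter. These points limit the size of the problem but leave the rule as it is.

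Three stronger readings are tempting, and the documents do not support them:

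- A reader might infer that a single blank trust item removes a participant. The wording fits one blank or all blank.
- A reader might infer that the rule cuts off the low-trust end of the sample. The Background presumes that trust modifies the label effect. It does not say that people with low trust skip trust questions.
- A reader might infer that the trust models themselves are biased and need multiple imputation as the primary method. If missingness depends on trust itself and not, given the covariates, on the choice, complete-case coefficients in a model that conditions on trust remain valid. Standard imputation assumes missingness depends only on observed data, so it can be biased in that very case. It is also awkward for a latent class model, where classes may swap labels between imputed datasets.

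Two cautions apply to the point as made here. The plan calls label and price the main attributes, not the only ones. It refers to the analysis without spelling out that every analysis is meant, though that is the natural reading when no model is exempted.

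**Conclusion.** The point holds as a contained, cheaply corrected weakness. As written, the rule removes participants whose response is complete under Section 18.0 from analyses that list no trust variable. That loss of choice data is avoidable.

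Its size cannot be fixed from the documents, which give no skip rate. Over an assumed range of 5% to 20% excluded, standard errors rise by 2.6% to 11.8%. The shift in the label estimate is zero if skipping is unrelated to trust and to choice. It was 3% to 6% in two illustrative differential scenarios, and 11% only in an extreme one with 30% against 5% skipping. Bias is therefore a plausible risk that the plan cannot detect, not something shown. Complete-case handling in the models that do use trust is acceptable.

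**What to change.** Amend the Missing Data paragraph as follows:

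1. Apply the trust-item exclusion only to models that use trust: the trust-adjusted logistic regression (including its exploratory variants) and the latent class analysis.
2. Keep every participant with a complete choice task in the multinomial and random-parameter models and in the paired t-test and ANOVA label comparisons.
3. State whether one blank trust item or all blank items trigger exclusion.
4. Report how many participants are excluded for missing trust answers, and compare them with those kept on sociodemographics, store and choices.
5. Keep complete-case as the primary method for the trust models, with multiple imputation as an optional sensitivity analysis.
6. Make AIC, BIC and log-likelihood comparisons involving the latent class model on the common complete-case subset.

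The number of choice scenarios should be reconciled at the same time, because it defines a complete choice task. The Phase 2 procedures say both 8 and nine, and the Analysis Plan says twelve.

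The cost is a change of wording, one descriptive table and a refit of the label and price models on the common subset for the fit comparison. Sample sizes will differ between models and must be reported with each. No new data are needed.
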